## Abstract

**Background:**

Developing effective prevention and intervention programs for the formative preschool years is seen as an essential step in combating the obesity epidemic across the lifespan. The overall goal of the current project is to measure the effectiveness of a healthy eating and childhood obesity prevention intervention, the MEND (Mind Exercise Nutrition Do It!) program that is delivered to parents of children aged 2-4 years.

**Methods/Design:**

This randomised controlled trial will be conducted with 200 parents and their 2-4 year old children who attend the MEND 2-4 program in metropolitan and regional Victoria. Parent-child dyads will attend ten 90-minute group workshops. These workshops focus on general nutrition, as well as physical activity and behaviours. They are typically held at community or maternal and child health centres and run by a MEND 2-4 trained program leader. Child eating habits, physical activity levels and parental behaviours and cognitions pertaining to nutrition and physical activity will be assessed at baseline, the end of the intervention, and at 6 and 12 months post the intervention. Informed consent will be obtained from all parents, who will then be randomly allocated to the intervention or wait-list control group.

**Discussion:**

Our study is the first RCT of a healthy eating and childhood obesity prevention intervention targeted specifically to Australian parents and their preschool children aged 2-4 years. It responds to the call by experts in the area of childhood obesity and child health that prevention of overweight in the formative preschool years should focus on parents, given that parental beliefs, attitudes, perceptions and behaviours appear to impact significantly on the development of early overweight. This is 'solution-oriented' rather than 'problem-oriented' research, with its focus being on prevention rather than intervention. If this is a positive trial, the MEND2-4 program can be implemented as a national program.

**Trial Registration:**

Australian New Zealand Clinical Trials Registry ACTRN12610000200088

## Background

Epidemiological studies indicate that childhood overweight is a serious problem in Australia, with an estimated 1 in 4 Australian school aged children and adolescents either overweight or obese [1]. Alarmingly, obesity is seen in even younger children, with rates of overweight and obesity almost doubling in a sample of 114,669 Australian 4-year-olds over the period 1995-2002 [2]. More recently, data from 4934 4- to 5-year-olds from the first wave of the nationally representative Longitudinal Study of Australian Children revealed that 15.3% of preschoolers were overweight and a further 5.2% obese [3]. Thus, the cost to society of obesity is high, with Access Economics estimating that the total annual cost of obesity to Australian society in 2008 was $58.2 billion, up from $21 billion in 2005 [4]. Furthermore, obesity in adults is strongly associated with the development of cardiovascular disease, type 2 diabetes mellitus and some cancers [5]. Overweight and obese children and adolescents are also at risk of a range of health problems and have an increased risk of premature death in adulthood; there are both immediate complications and long term consequences of child and adolescent obesity [6-8]. Research has shown that obesity can also have psychological consequences among children, such as increased stigmatization and depression [9,10]. The desire for thinness is present in girls as young as six years of age [11] and our research reveals that 4-year-old children are already concerned about their hair and clothes [12]. Higher weight status in 5-year-old girls has also been found to be associated with lower self-concept [13]; hence, preschoolers are at risk of obesity's negative psychological consequences.

Whilst strong evidence supports the role of non-modifiable genetic factors in energy storage patterns [14], these are insufficient to explain the increase in childhood overweight in recent years. Given that child weight is a multi-determined condition, researchers now argue that obesity prevention/intervention strategies must influence multiple determinants of child risk factors for overweight and obesity (i.e., increase in high-calorie, nutrient-poor food consumption, increase in sedentary behaviours, and a lack of physical activity, as well as parental attitudes and behaviours) [15,16]. The primary institution influencing preschool children is the family; consequently, many of the potentially modifiable determinants of risk factors for overweight and obesity in the preschool years will have roots within the family context [17]. Indeed, positive associations between certain aspects of parenting and preschool childhood overweight/obesity have been documented: parenting practices/behaviours and the beliefs supporting these strategies including maternal feeding practices, such as restricting access to foods and pressuring to eat [18-22]; reduced parental instrumental support for engagement in health promoting behaviours (e.g., not providing access or prompts for healthy eating or physical activity) [16,23]; low levels of parental modelling of healthy eating habits and physical activity [16,24,25]; and low parental nutritional knowledge [26].

In recent years, researchers have also examined the ways in which parents "*parent*" their children and found that particular parenting and feeding styles (i.e., authoritarian and permissive feeding styles) impact on young children's weight status [3,16,27,28]. Yet, despite widespread evidence that parenting behaviours, beliefs, and knowledge as well as parenting and feeding styles, are important in the development and maintenance of child obesity, relatively few studies have examined systematically whether targeting parental influences to modify these risk factors within a complex intervention will have an effect on weight status in preschool children.

Our systematic review ([name], [name], [name], [name], [name], [name]: Parental influence and obesity prevention in preschoolers: A systematic review of interventions, submitted) revealed that worldwide only eight RCTs have been conducted since 1995 on prevention of obesity in the 2-4 year old age group, and only one of these was conducted in Australia [29]; the age range targeted in this Australian study was 3-10 years, and the four-by-two-hour weekly group parent-education intervention program was for overweight children with a 3-month follow up period. This brief intervention for parents was effective in reducing childhood overweight at 3 months follow-up. Other studies have also shown that teaching parents about nutrition and healthy lifestyle behaviours results in improved knowledge [30] and health behaviours [15] and this can result in weight improvements for their children [31]. A key conclusion in the literature is the lack of translation of knowledge to action [32,33] and for this reason, future interventions should also specifically target strategies and techniques which parents can use to modify their child's dietary and physical activity patterns. It is argued that interventions that involve parents in a significant way may be particularly effective; they are likely to work by improving parental engagement, skills, and ability to provide opportunities for active play for their child and to create a healthy nutritional home environment [34].

The MEND (Mind, Exercise, Nutrition, Do It!) 2-4 program was designed to address this need for a healthy lifestyle program in the early years of childhood as well as a secondary obesity prevention initiative. MEND 2-4 is a 10-week community-based, multi-component healthy lifestyle program that is offered free to families with young children aged 2-4 years, irrespective of weight. The program aims to encourage healthy habits around diet and activity from an early age. It is a highly structured group program allowing parents to be supported in establishing healthy habits and making healthy behaviour changes at their own pace [35]. MEND 2-4 leaders are provided with comprehensive training by MEND Australia, and receive a leader's manual together with a full resource kit. The MEND 2-4 program is open to parents of children of any weight, although it is recommended that 'at risk' children be targeted (via referrals from General Practioners, Pediatricians, or Maternal and Child Health Nurses), including children who have/are: parental obesity, inactive and/or have poor eating habits, a risk of developing co-morbidities (e.g., family history of cardiovascular disease, type 2 diabetes, specific ethnic minorities). The overall goal of the current project is to measure the effectiveness of the MEND 2-4 program by conducting a randomised controlled trial (RCT).

## Methods/Design

### Overall study design

This study is a randomised controlled trial with parents of 2- to 4-year-olds randomly allocated to either the intervention or control groups and will be conducted and reported in line with CONSORT recommendations [36] (see Figure 1). Baseline assessment of study variables will occur at recruitment. Follow up assessments will take place at the end of the intervention (10 weeks post baseline measures) and at 6 and 12 months post intervention. This study was approved by the Deakin University Human Research Ethics Committee on the 7^th ^December 2009 (DU-HREC 2009-180).

**Figure 1 F1:**
[figure not shown]
**Study Design**. (attached as separate document).

### Hypotheses

In comparison to the wait-list control group, we predict that at the completion of the 10-week intervention program, and at 6 and 12 months post intervention, the intervention group preschoolers will: (1) demonstrate greater consumption of fruit and vegetables, and a decrease in consumption of high fat, high sugar cordials, soft-drinks and juices and non-essential, energy dense snack foods; (2) exhibit less problematic eating habits, specifically higher responsiveness to satiety, less fussiness, and less neophobia; (3) demonstrate greater increases in physical activity and greater decreases in time spent in sedentary behaviours, specifically TV viewing; (4) exhibit lower BMI-for-age z scores.

In comparison to the wait-list control group, we hypothesise at the completion of the intervention program, and at 6 and 12 months post intervention, the intervention group parents will: (1) increase the frequency with which they limit the offering of high fat, high sugar cordials, soft-drinks and juices and non-essential, energy dense snack foods to their child; (2) increase the frequency with which they offer vegetables and fruit, water and milk (rather than cordials, soft-drinks and juices) to their child; (3) demonstrate improved knowledge regarding key aspects of child eating, physical activity and sedentary behaviours relevant to the prevention of obesity and improving child health generally; (4) reduce the frequency with which they use restrictive feeding practices and increase the frequency with which they use covert methods of controlling access to unhealthy foods; (5) increase the frequency with which they model healthy behaviours around diet and physical activity; (6) provide greater opportunities for children to engage in physical activity and reduce their opportunities for engagement in sedentary behaviours.

### Participants

The participants will be 200 parents of 2-4 year old children. Parents will be eligible to take part if they can provide informed consent, are 18 years of age or older, and can read and write English. After assessment, parents who meet the inclusion criterion, and do not display exclusion criteria, will be randomly allocated to either the MEND 2-4 intervention (*n *= 100) or the wait-list control group (*n *= 100). A coded, double-blinded, variable-length permuted blocks randomised treatment allocation schedule produced by computer algorithm will be used.

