### Power, sample size, and retention

The primary outcome for this intervention is child eating habits and dietary intake. Both the expected clinical effect of the intervention and variability of the primary outcome measure are important considerations. Thus, sample size calculations were based on Australian data by Mathews et al. that provide relevant parameter estimates from three studies in the Barwon-South Western region of Victoria (*n *= 950) with children aged 2-4 years of age [60]. Vegetable consumption will require the largest sample size to demonstrate change over time, compared to other dietary outcomes, such as sweetened drinks, packaged snacks (e.g., chips, muesli bar), confectionary/chocolate, cake/sweet biscuits, and fruit, based on sample size analyses. As there are no quantitative dietary recommendations for children less than 4 years old in Australia, we adopted Campbell et al.'s suggestion of a 25% increase in vegetable consumption as a minimum target [61]. Based on Mathews et al.'s finding that 63% of pre-school children had ≤1 serve of vegetables per day [60], we assume that the intervention will have a 25% absolute effect, that is the proportion of children in the intervention group who only have ≤1 serve of vegetables per day will change from 63% to 43%. We calculated the sample size necessary to detect a clinically meaningful difference in vegetable consumption, significant at the 0.05 level, with a power of 0.8; this calculation resulted in a sample of 100 parents in each group. Making a prudent allowance for attrition of 20% (attrition in a large longitudinal study with multiple time points over a 3-year period by Clark et al. [62]) the adjusted number per treatment condition is 120. A total of 240 parents of 2-4 year old children will therefore be recruited at baseline to allow for a final sample of 200. The final sample size of 200 participants is also sufficient to detect medium effect sizes in the secondary measures with a power of 0.8 at α = 0.05 [63]. Every CI on this research team has had experience in retention of participants in longitudinal studies. To facilitate retention we will build rapport with the participants by a regular newsletter and advance notification of assessments. To increase retention rates the CIs have found two measures are very helpful: 1) Parents who remain in the study will be entered into prize draws for gift vouchers. The amount needs to include a large grand prize plus multiple minor prizes. Prizes will be drawn each year. 2) Birthday cards will be sent out to each child participant.

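### The number to randomise is 200 (100 per arm) in the abstract and Participants section but 240 (120 per arm) in the sample-size section; randomising 200 would leave about 80 per arm and 72% power

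*Protocol article*

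**What the plan says.** Three places in the protocol article give the size of the trial.

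- **Abstract, Methods/Design:** "This randomised controlled trial will be conducted with 200 parents and their 2-4 year old children". The same paragraph goes on to say that all parents consent and are then randomised.
- **Participants:** "The participants will be 200 parents of 2-4 year old children". Those who meet the eligibility criteria "will be randomly allocated to either the MEND 2-4 intervention (*n *= 100) or the wait-list control group (*n *= 100"). The computer-generated permuted-block schedule is described directly after this.
- **Power, sample size, and retention:** for 63% versus 43% of children having at most one serve of vegetables per day, at the 0.05 level with power 0.8, "this calculation resulted in a sample of 100 parents in each group". Then comes the attrition step, "Making a prudent allowance for attrition of 20"%, after which "the adjusted number per treatment condition is 120". The conclusion is "A total of 240 parents of 2-4 year old children will therefore be recruited at baseline to allow for a final sample of 200".

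**The concern.** In the Participants section, 200 is the number allocated. In the sample-size section, 200 is the number remaining after follow-up losses, and the number entering is 240. With any attrition at all these cannot both be true, and nothing in the text shown reconciles them.

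A recruitment target and an allocation schedule have to be set to one number. If the trial team works from the Participants section, the trial stops 40 families short and loses the whole attrition allowance. The study would then fall below its stated power for vegetable consumption, the outcome that the sample-size section says needs the largest sample. The hypotheses run to 12 months after the intervention, when losses will be greatest. The number allocated also defines the intention-to-treat population that the Analyses section commits to.

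**Working it through.** **Inputs, all from the sample-size section unless noted.** Proportions 0.63 and 0.43; alpha 0.05; power 0.80; attrition 20%; 100 per group before and 120 per group after the attrition allowance. The Participants section gives 100 randomised per arm. The number of sides is not stated; I assume two.

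**Step 1: reproduce the plan's 100 per group.** The mean proportion is (0.63 + 0.43)/2 = 0.53.

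n = [1.96·√(2·0.53·0.47) + 0.8416·√(0.63·0.37 + 0.43·0.57)]² / 0.20²

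= [1.96·0.7058 + 0.8416·0.6915]² / 0.04 = (1.3834 + 0.5820)² / 0.04 = 96.6, so 97 per arm.

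The stated 100 is this figure rounded up. The arcsine formula also gives 97, the unpooled formula 94 and the continuity-corrected formula 107. Other readings do not reproduce 100: a one-sided test needs 76 per arm (86 with continuity correction), and 63% versus 38% needs 62.

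**Step 2: reproduce the plan's 120 per group.** 100 × 1.20 = 120, and 2 × 120 = 240. So 120 is a number entering a treatment arm, with 100 as the number required at analysis.

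**Step 3: numbers left after 20% attrition.**

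- 100 randomised per arm: 100 × 0.8 = 80 per arm, 160 in total.
- 120 randomised per arm: 120 × 0.8 = 96 per arm, 192 in total.
- 125 randomised per arm (100/0.8): 125 × 0.8 = 100 per arm, 200 in total.

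**Step 4: power.** Power = Φ[(0.20·√n − 1.3834)/0.6915].

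| Randomised per arm | Left per arm | Argument of Φ | Power |
|---|---|---|---|
| 100 | 80 | (1.7889 − 1.3834)/0.6915 = 0.586 | 72.1% |
| 120 | 96 | (1.9596 − 1.3834)/0.6915 = 0.833 | 79.8% |
| 125 | 100 | (2.0000 − 1.3834)/0.6915 = 0.892 | 81.4% |

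At 80 per arm, other versions of the test give 72.3% (arcsine), 73.5% (unpooled) and 66.4% (continuity-corrected).

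**Step 5: how much loss 100 per arm can bear.** Power of 0.8 needs 97 per arm. Starting from 100, no more than 3 per arm (3%) can be lost.

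**The case against.** The best defence is that the attrition allowance was not overlooked. The sample-size section states it plainly with a recruitment figure, and the other two sections may simply repeat the analysable target loosely. A permuted-block schedule can be generated to any length, and nothing says it will stop at 200. That is a plausible account of how the wording arose, and it makes the power loss conditional on staff following the Participants section. It does not remove the conflict, because that section attaches 100 per arm directly to random allocation.

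Nor does it help to read 240 as recruited and 200 as randomised. The 120 is given per treatment condition, which a family joins only on allocation, and the 20% comes from a longitudinal study with repeated assessments, so it describes loss during follow-up.

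Other points have partial force:

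- The abstract does not tie 200 to allocation in the same sentence, so the firm conflict is between the Participants and sample-size sections. The abstract is supporting evidence.
- Figure 1 is not shown, and whether it gives numbers per arm is unknown.
- The 72% assumes the full 20% loss. The article reports low pilot attrition, so the real loss may be smaller. But 20% is the plan's own figure, and only 3% can be afforded.
- The planned analysis is covariate-adjusted and is repeated with multiple imputation. Earlier measurements may recover some lost information, but the article does not say how much, and the sample size was not calculated on that basis.
- At 80 per arm, power would be 81.8% one-sided, or 89.3% for 63% versus 38% (the 25-point effect described in words). Neither setting reproduces the stated 100 per group.

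**Conclusion.** The concern holds. The article states 100 randomised per arm in one section and 120 per arm in another, and only the second is consistent with its own attrition allowance. If 200 are randomised and 20% are lost, power for 63% versus 43% is about 72%, so the type II error rises from the intended 20% to about 28%. Randomising 240 gives 79.8%, essentially the stated 0.8.

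These figures rest on a two-sided 0.05 test, an unadjusted comparison of those with outcome data, the plan's 20% loss, and no allowance for clustering within program groups.

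A separate slip sits in the sample-size section: 240 × 0.8 = 192, so 240 does not yield the final 200 at 20% attrition. It does not change the conclusion, but it affects how the correction should be worded.

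**What to change.** State 240 randomised, 120 per arm, in the abstract and the Participants section, and generate the blocked allocation schedule for at least that number. Keep 200 only where it is clearly labelled as the target number with outcome data.

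In the same edit, settle the last step of the sample-size section. Either give the expected number with outcome data as 192 (96 per arm, 79.8% power), or, if 200 is meant literally at 20% attrition, randomise 200/0.8 = 250 (125 per arm, 81.4% power).

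The 240 option costs a change of wording in two places, plus correcting 200 to 192 in the sample-size section, and needs no recruitment beyond what is planned. The 250 option needs 10 more families. Either is easier to do before the allocation schedule is produced than after it has run out.

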### Recruitment strategies

Parent-child dyads will be recruited through local newspaper and kindergarten advertisements, maternal and child health centres, and general practice medical centres. Every effort will be made to include families from diverse ethnic backgrounds, given that different SES and ethnic groups exhibit differences in parental attitudes and beliefs in relation to feeding practices, child weight gain, and physical activity [37].

#### Procedure

##### The Intervention

The MEND 2-4 program involves 10 weekly 90 minute workshops relating to general nutrition, physical activity and behaviours, that are typically held at community health and maternal and child health centres, where parents and their preschool-aged children attend together. Each program group will consist of 6-10 child-parent dyads and a MEND 2-4 trained program leader. Program leaders, who are trained extensively by MEND Australia prior to starting with a group, will be monitored and evaluated by MEND Australia staff to ensure their practice is in accordance with MEND 2-4 guidelines; parental feedback on program leaders will also be obtained. Each session involves 30 minutes of guided active play, where parents can learn how to play with their children; 15 minutes of healthy snack time based on an evidence-based exposure-based technique to promote acceptance and increased intake of fruit and vegetables [38] and 45 minutes where the children participate in supervised crèche-style, creative play activities and concurrently the parents attend an interactive education and skill development session, based on evidence-based group-based parent-training principles [39]. Table 1 outlines the weekly education topics, and parents will receive handouts on these topics weekly. Pilot data reveals low attrition and that parents value the program and attend all 10 sessions. In the initial MEND 2-4 trials (UK) the participation rate was 87.6% which is high for developmental research [35].

**Table 1 T1:** Discussion topics and intervention content of MEND 2-4 program

Week	Workshop Title	Discussion Topic(s)	Intervention Content
1	**Welcome & introduction**	Meet the leader and pre-program measurements	Meet and welcome the families to their first MEND 2-4 physical activity and snack-time session; parents complete all pre-program forms and questionnaires and accurate child and parent anthropometric measurements (height and weight) taken.

2	**Introduction**	Introductions and individual expectations	Discussion of individual expectations and introduction of MEND 2-4 program and practicalities; Introduction of parents/carers to the behavioural model of parenting (customised as the 4Cs model (Causes, Consequences, Consistency and Copying) for the purposes of MEND 2-4).

3	**Healthy eating for families**	Healthy eating	Introduction to the five food groups, visual samples of excess sugar and fat found in foods. Discussion of appropriate treats and rewards and toddler intake of drinks.

4	**Be healthy, get active!**	Non-TV activities for toddlers	Importance of limiting TV watching among toddlers; Goal setting activity towards achievement of MEND 2-4 TV time guidelines (maximum of 1-2 hours of TV per day). Discussion of active play and activity ideas to replace time spent previously watching TV.

5	**What's in your child's food?**	Reading food labels	Reading food labels; MEND 2-4 label reading guidelines and identification of MEND 2-4 friendly food.

6	**Food without fuss**	Dealing with fussy eaters	Normalisation of fussy eating and common causes; importance of consistency around mealtimes and ideas for managing fussy eating behaviour. Strategies to reduce fear and unhelpful parenting behaviour around food at mealtimes.

7	**Portion sizes**	Healthy eating and portion sizes	Introduction to the MEND 2-4 portion sizes with visual demonstration; demonstration of difference between toddler and adult portion sizes.

8	**Fun with food**	Cooking together	Demonstration of ideas for making food preparation fun and including fruits and vegetables, how to actively involve children in preparation of snacks and parents/carers and child having fun with food together.

9	**Encouraging healthy habits**	Rules, routines and tantrum management	Establishing health as a priority within the family life-cycle. Helpful strategies for dealing with behaviours that may be resistant to change. MEND 2-4 sleep guidelines for toddlers.

10	**Farewell and graduation**	Evaluation and measurement	Collection of post-program measurements; MEND 2-4 certificates provided; information about follow-up activities or other local groups they may like to attend at the end of the MEND 2-4 Program.

